### Determination of sample size

This prospective, longitudinal cohort study will include 500 pregnant females. Given that we consecutively include participants, we judge this sample size as sufficient to generate estimates for the prevalence of perinatal depression, sleep disturbances, and sleep disorders during pregnancy and postpartum. Based on a meta-analysis of prevalence and incidence studies we expect the cumulative incidence of minor and major depression during late pregnancy and postpartum to be at least 20 % (*n* = 100). Taking into consideration that we plan to include 80 females in a trial of light treatment for the prevention of postpartum depression, we expect that approximately 300 females will be symptom free, while 100 to 150 females will experience minor or major depression during the perinatal period. For the study of risk factors involved into the development of perinatal depression, our sample size will enable the detection of small to moderate effects (d > 0.3) with an adequate statistical power (≥80 %).

For the Life-ON study no significance threshold a priori is considered.

The main outcomes of Life-ON 2 will be the change of depressive symptoms, response and remission rates after 6-week bright light treatment versus placebo. Based on a previous meta-analysis we expect that the prevalence of depression during the perinatal period will be at least 25 %, which would qualify 125 participants for inclusion in the treatment trial. From our previous experiences we anticipate an attrition rate of 25 % for reasons of refusal, non-compliance, or necessity for additional/alternative treatment. A conservative estimate would, therefore, be that 80 females will complete the treatment trial. At the same time, weekly monitoring is expected to increase compliance and reduce attrition and the available data suggests that prolongation of the treatment duration to 6 weeks will increase the bright light versus placebo difference. Our conservatively planned sample size (40 versus 40) will enable us to demonstrate medium effects (d >0.56) with a one-side error level of 0.05 and adequate statistical power (≥80 %).

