### Statistical analyses

Standard parametric or non-parametric statistical tests will be employed to explore differences between females with onset of depression to those remaining symptom free. To take full advantage of the longitudinal study design, generalized mixed modelling will be employed to test whether sleep-related and other fixed or variable markers can predict the onset of perinatal depression, possibly in a time-associated manner. The evaluation of BLT effectiveness for perinatal depression should take into account that this therapy will be applied at different times during the perinatal period; therefore, this will be included as a covariate in the ANCOVA (continuous data) and logistic regression analyses (dichotomous data, proportions). Regarding the efficacy of BLT in prevention of post-partum depression we will use logistic regression analysis to compare incidence rates between the group of not-depressed patients who received light therapy during pregnancy versus untreated subjects. For all analyses *p* values < 0.05 will be considered significant. The statistical analysis will be performed using a dedicated software (SPSS, IL, USA).

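### Life-ON 2 has three unranked main outcomes, each significant at p < 0.05, so the chance of a false-positive main result is about 10–12 %, and the power statement covers only one of them

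*Protocol article*

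**What the plan says.** The section on determination of sample size in the protocol article lists the Life-ON 2 endpoints together: "The main outcomes of Life-ON 2 will be the change of depressive symptoms, response and remission rates after 6-week bright light treatment versus placebo". None is called primary and no order is given.

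The same section sizes the trial once. "Our conservatively planned sample size (40 versus 40") is said to be a number that "will enable us to demonstrate medium effects (d >0.56"), "with a one-side error level of 0.05 and adequate statistical power (≥80" %). No response or remission rates are assumed.

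The section on statistical analyses plans ANCOVA for continuous data and logistic regression for proportions, with the time at which light treatment was given as a covariate: "therefore, this will be included as a covariate in the ANCOVA (continuous data"). It closes with a rule for all analyses, under which p "values < 0.05 will be considered significant". The article contains no multiplicity procedure and no joint success rule.

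**The concern.** Life-ON 2 is the randomised, placebo-controlled part of the project, and its result will be read as evidence for or against efficacy. With three co-equal main outcomes and a flat threshold, a result significant on only one of them could be reported as a positive trial. The error rate of that decision is the chance that at least one of three tests is falsely significant, and that exceeds the 5 % used to size the trial.

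The sizing statement is also easy to read as covering all three outcomes, because it follows directly after them in the same paragraph. It is expressed as a standardised mean difference, so it says nothing about the two rates. A dichotomised outcome normally carries less information than the score behind it, so a trial sized for the score has less power for response or remission.

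**Working it through.** **Inputs from the article.** Three main outcomes; significance at p < 0.05 for all analyses; 40 per arm; d = 0.56; one-sided 0.05; power at least 80 %; 1:1 allocation.

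**Step 1. The stated figure.** For two means with n per arm, the expected z is d·√(n/2) = 0.56 × √20 = 2.504. One-sided power by the normal approximation is Φ(2.504 − 1.645) = Φ(0.859) = 80.5 %. The noncentral t gives 79.9 %, with a smallest detectable d of 0.561. The figure is right for a continuous outcome.

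**Step 2. False positives over three tests.**

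- Independent tests: 1 − 0.95³ = 1 − 0.857 = 14.3 %. The Bonferroni bound is 3 × 0.05 = 15 %.
- Equally correlated z statistics, one-sided at 1.645: 11.8 % at correlation 0.5 and 9.3 % at 0.8. Two-sided at 1.96: 12.5 % and 9.8 %.
- All three outcomes from one scale, simulated with no treatment effect (20,000 trials, 40 per arm). Assumptions: baseline mean 18, SD 4; week-6 mean 10, SD 6; response is a reduction of at least 50 %; remission is a score of 7 or less; baseline-to-week-6 correlation 0.3, 0.5 or 0.7. The chance of at least one significant result was 10.4–10.6 % one-sided and 11.1–11.5 % two-sided. Each single test stayed close to its nominal level (4.6–5.7 %).

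A realistic range is therefore about 10–12 %, roughly twice the nominal 5 %. It hardly depends on whether the tests are one- or two-sided.

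**Step 3. Power for the two rates.** The article gives no rates, so control rates p₀ of 30, 40 and 50 % are assumed. The effect d = 0.56 is carried over by a probit shift, p₁ = Φ(Φ⁻¹(p₀) + 0.56). With p̄ = (p₀ + p₁)/2, s₀ = √(2p̄(1 − p̄)/40) and s₁ = √((p₀(1 − p₀) + p₁(1 − p₁))/40), one-sided power is Φ((p₁ − p₀ − 1.645·s₀)/s₁). The last column replaces s₀ by s₁.

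| p₀ | p₁ | s₀ | s₁ | Power, pooled SE | Power, unpooled SE |
|---|---|---|---|---|---|
| 0.30 | 0.514 | 0.110 | 0.107 | 62.3 % | 63.8 % |
| 0.40 | 0.620 | 0.112 | 0.109 | 63.1 % | 64.7 % |
| 0.50 | 0.712 | 0.109 | 0.107 | 62.0 % | 63.5 % |

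Response or remission taken alone thus has about 62–65 % one-sided power where the continuous outcome has 80 %. Two-sided at 0.05, the same formulas give about 49–52 %.

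**Step 4. Cost of two remedies.** A Bonferroni split uses 0.05/3 = 0.0167. At d = 0.56 and 40 per arm, one-sided power for the continuous outcome falls to 63 %, and 80 % would need 57 per arm. A single primary outcome keeps 0.05 and 40 per arm.

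**The case against.** The strongest reply is that a condensed article commonly leaves outcome ordering and multiplicity to the full protocol or analysis plan, and that Life-ON 2 serves a secondary aim of the project. It is also true that nowhere does the article say that any one outcome suffices. If all three had to succeed, there would be no inflation. This limits the claim to a conditional one but does not remove it. The article is not silent here: it names three main outcomes together and fixes one threshold for all analyses, and a reader applying that text gets the error rates above. For Life-ON 3, by contrast, it names a single main outcome.

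Four stronger readings are tempting, and the documents do not support them.

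- **Precision is thrown away because baseline is left out of the ANCOVA.** The article names timing as a covariate without making it the only one, and it neither names nor excludes the baseline score. A full covariate list is ordinary analysis-plan content. Omitting baseline would cost power but would neither bias a randomised comparison nor raise its type I error. Any gain also depends on a correlation r that is not given. Against an unadjusted change score with equal SDs, the variance factor is (1 + r)/2. Two-sided power at d = 0.56 would then rise from 70 % to 87, 81 or 77 % for r = 0.3, 0.5 or 0.7.
- **The error rate is worse because there are four depression scales to choose from.** The EPDS, VAS, HDRS-21 and MADRS appear in a tool list for the whole project (Table 3). Nothing says that all four are Life-ON 2 efficacy outcomes.
- **The false-positive rate is 14 %.** That needs independent outcomes, which is implausible because response and remission are normally derived from the same score as the change.
- **The sample size is wrong.** It reproduces. Sizing on one outcome is ordinary practice, and the article claims no power for the rates.

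**Conclusion.** The point holds in limited form. Three unranked main outcomes, one threshold of 0.05 and no success rule give about a 10–12 % chance of at least one false-positive main result, provided that any one outcome may support efficacy. That range rests on correlated outcomes, either simulated from one scale or set at a correlation of about 0.5; it falls to about 9 % at a correlation of 0.8.

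The stated power is correct for the continuous outcome and silent on the other two. The 62–65 % for response or remission rests on assumed control rates and a probit shift. It supports choosing a single primary outcome but is not a separate error in the plan. On baseline adjustment, the text supports a request for confirmation and nothing more.

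**What to change.** 1. Name 6-week change on one stated depression scale as the single primary outcome of Life-ON 2.
2. Test response and remission after it in a fixed order, each only if the preceding test succeeds, or label both secondary.
3. State that d > 0.56 with 40 versus 40 refers to the continuous outcome only.
4. Confirm that the ANCOVA includes the baseline score on the chosen scale alongside treatment timing.

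This changes analysis wording only and adds no participants, whereas a Bonferroni split would need 57 per arm one-sided. The downside is that response or remission alone could no longer support the efficacy claim.

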### Null hypothesis

Neither subjective or polysomnographic sleep features or sleep disorders can be related to development of PND. BLT is not effective in preventing or treating PND.

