• MINI-International Neuropsychiatric Interview (MINI), clinician rated [53] • MINI-International Neuropsychiatric Interview Plus (MINI Plus), clinician rated • Edinburgh Postnatal Depression Scale (EPDS), self-administered (depression > 12) [54] • Visual Analog Scale for depression (VAS), self-administered (ranging between 0 and 10) [55] • Hamilton Depression Rating Scale - 21 items (HDRS-21), clinician-rated (14–18 = moderate depression, 19–22 = severe depression, ≥ 23 = very severe depression) [56] • Montgomery-Asberg Depression Rating Scale (MADRS), clinician-rated (normal 0–6; mild depression 7–19; moderate depression 20–34; severe depression >34) [57] • Temperament and Character Inventory (TCI), self-administered [58] _•_ Interview for Recent Life Events (IRLE), self-administered [59]
Sleep assessment tools
• Pittsburgh Sleep Quality Index (PSQI), self-administered (good sleeper <5; poor sleeper ≥5) [60] • Insomnia Severity Index (ISI), self-administered [normal ≤7; sub threshold insomnia 8–14; clinical insomnia (moderate severity) 15–21; clinical insomnia (severe) 22–28] [61] • Epworth Sleepiness Scale (ESS), self-administered (normal <10; pathological ≥ 10) [62] • RLS interview (5 criteria), clinician rated [63] and the International RLS Study Group Rating Scale (if RLS diagnosed) [64] • Munich Parasomnia Screening (MUPS), self-administered [65] • Morningness-Eveningness Questionnaire (MEQ), self-administered (16–30 “definite evening types”, 31–41 “moderate evening types”, 42–58 “intermediate types”, 59–69 “moderate morning types”, 70–86 “definite morning types”) [66] • One night of home polysomnography (PSG) • Wrist Actigraphy (7-days of consecutive home recording)

Pregnant women, who will have accepted to participate in the main observational Life-ON study, will also be asked to additionally and voluntarily take in part in the Life-ON 1 substudy (genetic investigation). The substudy Life-ON 2 will be proposed to women who develop PND during pregnancy or during the 9 months’ period after delivery. A random population of non-depressed pregnant women will be asked to participate in the preventive BLT trial Life-ON 3 (substudy). A specific dedicated written informed consent is necessary to participate in each of the above mentioned substudy, and woman can withdraw their consent at any time (Fig. 1).

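### Life-ON 2 has three unranked main outcomes on no named scale, each judged at an unadjusted p < 0.05, but is sized for one continuous test

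*Protocol article*

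**What the plan says.** All references are to the protocol article.

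- **Determination of sample size** gives the endpoints of Life-ON 2: "The main outcomes of Life-ON 2 will be the change of depressive symptoms, response and remission rates after 6-week bright light treatment versus placebo". No order, primary outcome or success rule follows. The same section says that 40 versus 40 "will enable us to demonstrate medium effects (d >0.56") and sets this "with a one-side error level of 0.05 and adequate statistical power (≥80" %). An effect size d applies to a continuous outcome, so this describes one comparison of means.
- **Table 3** lists four measures of depressive severity for the project: EPDS, a VAS for depression, HDRS-21 and, for example, "Montgomery-Asberg Depression Rating Scale (MADRS), clinician-rated". None is assigned to the Life-ON 2 outcomes. In the section on substudy Life-ON 2, EPDS appears only as an entry criterion.
- **Statistical analyses** plans ANCOVA for continuous data and logistic regression for proportions, with one threshold for all analyses: p "values < 0.05 will be considered significant". Sidedness is not given there.
- **Null hypothesis** puts the treatment question as one statement: "BLT is not effective in preventing or treating PND".

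**The concern.** The sizing statement promises a 5 % one-sided error for one test. The text names three main outcomes and lets each be called significant at 0.05. It does not say which result, or which combination, would reject the null. If any one is enough, the 5 % no longer describes the claim that bright light treats perinatal depression.

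The open choice of scale adds to this. The four measures mix self-administered and clinician-rated tools in a single-blind trial, so they need not agree. The article's own Table 1 shows results varying by scale. In the double-blind antenatal trial of 26 women, improvement was 58 % versus 41 % on one scale (a gap of 17 points) and 64 % versus 38 % on HDRS (26 points).

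Life-ON 2 is the project's only placebo-controlled efficacy test, since Life-ON 3 is open-label against no treatment. The article waives an a priori significance threshold for the observational Life-ON study only, so Life-ON 2 is meant to be tested formally.

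**Working it through.** **1. Reproduce the sizing.** Inputs from Determination of sample size: 40 per arm, d = 0.56, one-sided 0.05, power at least 80 %.

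- n per arm = 2(1.645 + 0.842)² / 0.56² ≈ 39.4, so 40.
- Power at n = 40: Φ(0.56 × √(40/2) − 1.645) = Φ(2.504 − 1.645) = Φ(0.86) ≈ 80.5 %. The exact noncentral t gives 79.9 %.
- The same comparison at two-sided 0.05 has 69.6 % power (exact t), and the effect detectable with 80 % power is d = 0.63.

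The stated size is right for one one-sided comparison of means. It says nothing about response or remission. With assumed rates of 50 % versus 30 %, for illustration, 40 per arm gives about 57 % power at one-sided 0.05.

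**2. Bounds if any one test counts as a win.** If independent: 1 − 0.95³ = 14.3 % for three tests and 1 − 0.95¹² = 46 % for twelve (3 outcomes × 4 scales). The tests are correlated, so these are too high.

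**3. Simulation under no effect.** 20,000 trials with 40 per arm: baseline-adjusted ANCOVA for change, and two-proportion tests standing in for logistic regression. Assumptions not in the documents: baseline 18 (SD 4), follow-up 10 (SD 6), baseline to follow-up correlation 0.4, response as a fall of at least 50 %, remission as a score of 7 or less, and inter-scale correlation as shown. Chance of at least one significant result in favour of bright light:

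| Inter-scale correlation | Threshold | Change, one scale | Three outcomes, one scale | Change, four scales | All 12 tests |
|---|---|---|---|---|---|
| 0.5 | one-sided 0.05 | 5.0 % | 9.9 % | 14.5 % | 27.3 % |
| 0.7 | one-sided 0.05 | 5.0 % | 9.6 % | 11.8 % | 23.5 % |
| 0.85 | one-sided 0.05 | 4.8 % | 9.7 % | 9.5 % | 20.5 % |
| 0.5 | two-sided 0.05 | 2.4 % | 5.1 % | 7.6 % | 15.9 % |
| 0.7 | two-sided 0.05 | 2.5 % | 5.2 % | 6.3 % | 13.8 % |
| 0.85 | two-sided 0.05 | 2.4 % | 5.2 % | 5.2 % | 12.1 % |

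A repeat simulation gave about 10 % (one scale, one-sided), about 6 % (one scale, two-sided) and 21 to 28 % (12 tests, one-sided). As a cross-check, the three test statistics on one scale correlated at about 0.7 to 0.8. Three normal statistics with equal correlations of 0.7 and 0.8 give 10.2 % and 9.2 % at one-sided 0.05.

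**4. Compare the remedies.**

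- Bonferroni over three outcomes (one-sided 0.05/3): power at d = 0.56 falls to 63.3 % (exact t), and n = 2(2.128 + 0.842)² / 0.56² ≈ 56.2, so 57 per arm for 80 %.
- Fixed sequence with one primary outcome: under no effect, nothing is declared unless the first test rejects, so the error stays at 5 %. Power for the primary stays at about 80 % with 40 per arm.

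**The case against.** Several points on the other side stand.

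- **No decision rule is written.** A reader might infer that any single significant result proves efficacy under the plan. The documents do not say so. If all three outcomes had to be significant, there would be no inflation.
- **Twelve tests is a ceiling.** A reader might infer that about one trial in four would give a false benefit. Table 3 lists tools for the whole project, and the article refers the cohort's assessment schedule to a supplementary table that is not at hand. Nothing shown says that all four scales are taken at baseline and week 6 of Life-ON 2. For the VAS, Table 3 gives a range but no cut-off.
- **Inflation far above 5 % is not established.** On one scale, the one-sided figure is a doubling. If p < 0.05 is two-sided, false benefit is about 5 to 6 %, close to the error level in the sizing statement, although twice the nominal 2.5 % for that direction.
- **The sample size is not wrong.** It reproduces, and its use of d hints that symptom change is the outcome the trial was built on.
- **An article condenses.** Definitions of response and remission, and the choice of scale, are commonly left to a fuller document. Life-ON 2 also serves a secondary aim.

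These points limit the size of the problem but do not remove it. The article itself gives three outcomes equal standing and sets one unadjusted threshold for every analysis, so a later plan that ranked or adjusted would have to depart from it. For Life-ON 3, the same article names a single main outcome.

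**Conclusion.** The point holds in limited form and should be corrected. Three unranked main outcomes, no named scale and an unadjusted 0.05 do not match a sample size that covers one continuous test.

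The size depends on an assumed rule that any significant main outcome counts as benefit. On one scale, the false-benefit rate is then about 10 % at one-sided 0.05, or about 5 to 6 % if the threshold is two-sided (nominal 2.5 %). The 21 to 28 % range (one-sided) applies only if all three outcomes were tested on all four scales, with an assumed inter-scale correlation of 0.5 to about 0.8. The score distributions and the response and remission cut-offs are also assumed.

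**What to change.** Before any outcome data are examined, state the following. In a single-blind trial, a deadline tied to unblinding would be a weak safeguard.

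1. The single primary outcome is the 6-week change on one named depression scale assessed in Life-ON 2, tested by the planned ANCOVA at the full one-sided 0.05 used for sizing.
2. Response, then remission, on that same scale are tested in fixed sequence, each only if the test before it is significant.
3. Other scales are reported with intervals only.
4. The same sidedness appears in Determination of sample size and in Statistical analyses. If two-sided 0.05 were chosen instead, power at d = 0.56 would be about 70 % and the sizing statement would need revision.

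The cost is a paragraph of wording and no added participants, against 57 per arm under a Bonferroni split. The downside is that a significant response or remission result alone would no longer support an efficacy claim.

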Concerning the substudy Life-ON 3, previous meta-analyses have estimated an incidence of 15 to 49 % for the onset of minor and major depression during a 12 months’ postpartum period. Our sample size calculation is based on an assumed incidence of 20 % in females receiving no treatment and we expect this incidence to be reduced to 5 % in females receiving bright light treatment during late pregnancy. With a planned allocation ratio of 1:3 and a one-sided alpha level of 0.05, comparison of 43 treated females to 172 untreated subjects will yield an adequate statistical power (≥80 %). Assuming an even lower incidence of 15 % in untreated subjects, sample size calculations indicate that inclusion of 79 vs. 314 subjects will be needed to demonstrate a reduced incidence (5 %) with adequate statistical power. We therefore plan to block-randomise consecutive participants on a 1:3 basis to BTL versus no treatment until 80 participants have received active light treatment.

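### Life-ON 3 states a 1:3 allocation, but its printed sample sizes (43 vs 172 and 79 vs 314) are 1:4; the ratio, sizes and power need to be made consistent, although the effect on power is small

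*Protocol article*

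**What the plan says.** All the relevant text is in one paragraph on Life-ON 3 in the Protocol article, Determination of sample size.

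- Base case: "Our sample size calculation is based on an assumed incidence of 20 % in females receiving no treatment". Light therapy is assumed to lower that figure to 5 %.
- Ratio, error level and size for the base case: "With a planned allocation ratio of 1:3 and a one-sided alpha level of 0.05, comparison of 43 treated females to 172 untreated subjects", for which at least 80 % power is claimed.
- Lower-incidence scenario, 15 % untreated against 5 % treated: "sample size calculations indicate that inclusion of 79 vs. 314 subjects will be needed".
- Randomisation rule drawn from these figures: "We therefore plan to block-randomise consecutive participants on a 1:3 basis to BTL versus no treatment until 80 participants have received active light treatment".

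The ratio 1:3 is therefore given twice, once as an input to the calculation and once as the rule for the randomisation list. The Statistical analyses section names logistic regression for this comparison. The sample-size section does not name the test behind the calculation.

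**The concern.** Neither printed pair has the ratio that the text gives for it, and the last sentence does not follow from the one before. The plan says 314 untreated women are needed, then on that basis adopts a rule that delivers about 240. Someone preparing the randomisation list or checking accrual cannot tell from this paragraph whether the comparator group should have about 240 or about 320 women. The power claim is also attached to sizes that the stated ratio does not produce. At stake are a correct statement of the comparator size in a randomised comparison, and a power figure that belongs to the design actually run.

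**Working it through.** **Inputs** (all from the Life-ON 3 paragraph): incidence 5 % treated; 20 % or 15 % untreated; one-sided alpha 0.05; target power 80 %; stated ratio 1:3; printed sizes 43 vs 172 and 79 vs 314; recruitment until 80 are treated. No drop-out is applied, since none is stated for this substudy.

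**Step 1: ratios.** 172/43 = 4.00 and 314/79 = 3.97. At 1:3 the untreated groups would be 3 × 43 = 129 and 3 × 79 = 237. The gap is too large for rounding.

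**Step 2: reproduce the plan's figures.** Exact power of a one-sided Fisher test is the sum, over all outcomes (x events among n1 treated, y among n2 untreated), of Bin(x; n1, 0.05) × Bin(y; n2, p0), counting only outcomes whose hypergeometric tail probability P(X ≤ x | x + y) is at most 0.05.

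A search over total size at 1:4, with n1 rounded to the nearest whole number, first reaches 80 % at these totals:

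- 20 % vs 5 %: 215, that is 43 vs 172, power 80.3 % (42 vs 168 gives 79.1 %).
- 15 % vs 5 %: 393, that is 79 vs 314, power 80.4 % (78 vs 312 gives 78.9 %).

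Both printed pairs come back exactly. At 1:3 no method tried gives 172 or 314 untreated women:

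| Method at 1:3 | Untreated, 20 % case | Untreated, 15 % case |
|---|---|---|
| Pooled z, one-sided | 126 | 234 |
| Pooled z with continuity correction, one-sided | 153 | 273 |
| Fisher, one-sided, smallest total | 136 | 248 |
| Pooled z, two-sided | 162 | 303 |

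**Step 3: what the randomisation rule delivers.** 80 × 3 = 240 untreated women. 314 − 240 = 74, and 74/314 = 24 % fewer than the number said to be needed.

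**Step 4: power at the relevant sizes** (one-sided 0.05).

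| Sizes | Scenario | Fisher | Score test (exact power) |
|---|---|---|---|
| 80 vs 240 (1:3 as randomised) | 15 % vs 5 % | 78.8 % | 82.1 % |
| 80 vs 240 (1:3 as randomised) | 20 % vs 5 % | 97.0 % | 97.9 % |
| 80 vs 320 (1:4) | 15 % vs 5 % | 80.1 % | 84.7 % |

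A hand check with the pooled normal formula, power = Φ[(d − 1.645 × SE0)/SE1], for 80 vs 240 at 15 % vs 5 %:

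- Pooled proportion = (4 + 36)/320 = 0.125.
- SE0 = √[0.125 × 0.875 × (1/80 + 1/240)] = 0.0427.
- SE1 = √(0.0475/80 + 0.1275/240) = 0.0335.
- Power = Φ[(0.10 − 0.0702)/0.0335] = Φ(0.89) = 81.3 %.

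**Step 5: Fisher minima at exactly 1:3.** 20 % vs 5 %: 47 vs 141 (80.1 %; 46 vs 138 gives 79.6 %). 15 % vs 5 %: 83 vs 249 (80.5 %; 82 vs 246 gives just under 80 %).

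**The case against.** The strongest reply is that little depends on this. The Fisher test is inferred from the match and is not named in the plan. The named analysis is logistic regression, and at 80 vs 240 for 15 % vs 5 % the unadjusted one-sided logistic tests have exact power of 80.0 % (Wald), 82.1 % (score) and 84.9 % (likelihood ratio). The scenario on which the plan says its calculation rests, 20 % vs 5 %, keeps about 97 %. The target of 80 treated women need not change under either ratio. All of this stands, and it limits the consequence. It does not remove the contradiction.

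A second reply is that 172 and 314 might be totals at 1:3, since 172/4 = 43 and 314/4 = 78.5. The text, however, describes the 172 as untreated women: "comparison of 43 treated females to 172 untreated subjects will yield an adequate statistical power (≥80". On the totals reading the paragraph would still be misprinted, because the untreated groups would then be 129 and about 235.

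A reader might go further and infer that the prevention trial is materially underpowered. The documents do not support that: the only shortfall is 1.2 points, under one unnamed test, in the less favourable scenario. Nor can the 25 % attrition rate given for Life-ON 2 be used to enlarge it. That rate covers refusal, non-compliance and need for other treatment among depressed women in a treatment trial. Life-ON 3 has an untreated arm and recruits until 80 women have actually received light. Recomputing at a two-sided level would raise a different question, because the plan fixes "a one-sided alpha level of 0.05" here and sidedness affects any ratio alike.

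**Conclusion.** The paragraph is wrong as written: a 1:3 ratio stated twice cannot stand with two size pairs that are 1:4, and no reading makes all its figures agree. The exact match at 1:4 in both scenarios is strong evidence that the calculation was run at 1:4, but it does not show which ratio was intended for the trial. Under the stated rule the comparator group is about 240 women, 74 fewer than the plan says it needs. The power consequence is minor: against the 80 % target, 78.8 % by Fisher or about 82 % by a score test for 15 % vs 5 %, and about 97 % for 20 % vs 5 %. These figures assume the plan's own incidences, one-sided alpha 0.05, an unadjusted comparison and no loss to follow-up. The point is an error in a core design figure that needs correcting. It is not a finding that the trial lacks power.

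**What to change.** State one allocation ratio throughout, name the test behind the calculation, and make sizes and power follow from them. Either of two corrections would do, and the sponsor must say which was intended.

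1. **Keep 1:3.** State that 80 vs 240 women will be randomised. Give the power at that size: 78.8 % by one-sided Fisher or about 82 % by a score test for 15 % vs 5 %, and about 97 % for 20 % vs 5 %. Replace the printed pairs with 1:3 values (by Fisher, 47 vs 141 and 83 vs 249). If 80 treated women is kept and Fisher is the named test, the claim of at least 80 % for the 15 % scenario should be softened accordingly.
2. **Adopt 1:4.** Change both ratio statements. The sizes become 80 vs 320, with 80.1 % power by Fisher for 15 % vs 5 %. Check that 80 + 320 = 400 non-depressed women can be recruited from the cohort of 500, of whom the plan expects 100 to 150 to become depressed at some point in the perinatal period. The 1:3 design needs 320.

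The first option costs only wording and a slightly less favourable power statement. The second also requires the randomisation list to be built at 1:4 and leaves less room for refusal.
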